### Eligibility criteria {10}

#### Inclusion criteria

The inclusion criteria will be as follows: literate individuals (those who can read and write) of both sexes, aged 18 years or older, with a medical diagnosis of fibromyalgia, proven by the International Statistical Classification of Diseases and Related Health Problems (ICD-10), with code M79.7, and confirmed by an evaluator according to the ACR Classification Criteria, revised 2016 version. In addition individuals with suitable electronic devices and internet access, preserved speech and hearing capacity, which allow the application of questionnaires.

#### Exclusion criteria

The exclusion criteria will be as follows: diagnosis of other conditions causing chronic pain (neuropathies, rheumatoid arthritis, osteoarthritis, spinal stenosis, or neoplasia); medically proven severe mental disorders (schizophrenia, psychosis, bipolar affective disorder, severe depression); individuals with visual or hearing impairments.

### Who will take informed consent? {26a}

Subjects will be instructed verbally and in writing about their participation in the study before signing the Informed Consent Form.

### Additional consent provisions for collection and use of participant data and biological specimens {26b}

This trial does not involve collecting biological specimens for storage.

## Interventions

### Explanation for the choice of comparators {6b}

Web-based educational intervention associated with physical exercise compared with simple educational material. The reasons for choosing interventions are according to the European Alliance of Associations for Rheumatology (EULAR), because it recommends the use of non-pharmacological therapies as a first-line intervention for patients with fibromyalgia, with patient education and physical exercise being a combination indispensable in the management of symptoms [10]. First, the experimental group comes from the purpose that physical exercise is one of the most accepted modalities. Studies have shown that physical exercise was well tolerated by patients with fibromyalgia. These studies achieved positive effects on pain intensity, fibromyalgia impact, hyperalgesia, physical function, catastrophizing, and psychological distress, without major adverse events [11–15]. In addition, health education is one of the main items to enable the promotion of the health of patients with fibromyalgia, because this strategy must prepare people to take control and responsibility for their own health and the health of their environment, as well as prepare them for empowerment, decision-making, participation, social control, and action on the conditions and determinants of their health and quality of life [16–18]. Regarding the choice of comparing with only one educational material (e-book), the proposal was due to the fact that the material has already been validated and published and showed a good level of agreement between the evaluators [31]. Thus, this type of intervention only includes health education and is not associated with physical exercise. Both programs (Amigos de Fibro and the e-book) were developed in Brazil by the authors. In addition, both are in Portuguese (Brazilian) language and are available in open access for consultation.

### Intervention description {11a}

#### Study groups

##### Intervention

The meetings will be organized by two physiotherapists, who will invite a multidisciplinary team working in primary care to give lectures and hold debates, rounds of conversation and exercises through the Google Meet platform. In addition, a physiotherapist will apply the physical exercises described in “Amigos de Fibro (Fibro Friends)”. The invited professionals will be as follows: a physiotherapist, a physician, a psychologist, a nutritionist, a nurse, a pharmacist, a speech therapist, an occupational therapist, a social worker, and a naturologist.

The activities will be conducted through an online group. In health promotion, group work makes it possible to break the vertical relationship that traditionally exists between the health professional and the subject of their action, which is a strategy that facilitates the expression of needs, expectations, anxieties, and life circumstances, which have some impact on the health of individuals and groups. Moreover, when developing the work with groups, the professional has the chance to stimulate participants to find collective strategies to confront the problems the community faces [32]. When starting a group, the uncertainties of the participants must be considered and, therefore, it is necessary to create a safe and reliable environment [33]. It is necessary to consider that, at this moment, introductions are formal and moments of silence are common [34]. It will be necessary to observe the group’s expectations and non-verbal communication, stimulate group cohesion and keep the group’s objectives clear, relating them to the members’ needs. At this time, it is also important to establish and maintain schedules, meeting locations and a limit of participants [34]. Participants will also be informed to avoid opening new tabs or web pages, other applications, and/or other distractions at the time of the meeting.

The language should be clear and easy to understand for the group at hand. These details can facilitate the group’s dynamics and good functioning and, consequently, obtain better results. Communication and empathy are also necessary [34]. Only effective communication can help the patient conceptualize their problems, face them, envision their participation in the experience, and alternative solutions for them, seeking to adapt to new patterns of behavior. Empathy refers to an emotional attunement of the coordinator with the participants—integrating into the group atmosphere [34].

Each meeting must be structuralized in, at least, three basic moments: an initial moment of group preparation for the work of the day (team-building exercises, warm-ups, relaxation); an intermediary, where the group is involved in a variety of activities that facilitate their reflection and elaboration of the developed subject; and a moment of systematization and evaluation of the work of the day that allows the participants to visualize their production as a workgroup [35]. In addition, this program will be based on the cognitive behavioral therapy model, which is one of the therapies that act on the effects regarding behavior, emotions, and symptoms. This approach has an emphasis on the current situation of the individual rather than on past situations [36–38]. Thoughts may represent cognitive changes that directly influence the health condition of the individual. In this sense, this therapy seeks to change the behavioral aspects of the individual by stimulating them to review inappropriate attitudes and beliefs that may negatively influence the health condition of these individuals [36–39].

Regarding the physical exercises that should be included in the treatment of individuals with fibromyalgia [10], a recent review on physical exercises for fibromyalgia published in the Cochrane Database of Systematic Review [40] highlights that no evidence was found of improvement in pain superior to that of the study by Assumpção et al. [41], where improvement was at 30%. In this sense, we chose to use the aforementioned protocol [41], which meets the guidelines of the European Alliance of Associations for Rheumatology [10], highlighting that for non-pharmacological interventions in the management of fibromyalgia, patient education is indicated, in association with physical exercise. Assumpção et al. [41] suggest the inclusion of both approaches in exercise therapy programs for fibromyalgia in clinical practice.

Exercise sessions should be performed online with an approximate duration of 40 min each, once a week, for flexibility and low-intensity strengthening exercises [41]. Participants will be instructed to position themselves correctly to perform the exercises and, at all times, correct body alignment awareness will be emphasized [41]. The physical exercises will be interspersed: muscle stretching 1 week, and muscle strengthening the other. Participants will be tended to online as a group and under the guidance of a physiotherapist. Figure 2 presents the structure of the physical exercise program, based on Assumpção et al. [41] and the American College of Sports Medicine (ACSM) [42].

**Fig. 2 Fig2:**
[figure not shown]
“Amigos de Fibro (Fibro Friends)” physical exercise program

It is important to note that we considered the new version of guidelines on physical activity created by the World Health Organization in 2020 [43]. In this sense, the current guidelines recommend that all adults and elderly individuals with chronic conditions should perform at least 150 to 300 min of moderate-intensity aerial physical activity; or at least 75 to 150 min of vigorous-intensity aerial physical activity; or an equivalent combination of moderate-intensity and vigorous-intensity physical activities throughout the week for substantial health benefits [43]. So, considering that fibromyalgia is a chronic pain syndrome that has an important negative impact on the quality of life of patients, all participants will be instructed on the frequency and time of physical activities that should be performed per week and encouraged to perform them at home, in addition to what was proposed in the web-based program, to ensure the benefits of regular physical activity [43].

The “Amigos de Fibro (Fibro Friends)” program will be conducted by the invited professionals, according to the themes of each meeting that were developed in the first phase of the study, based on the National Health Promotion Policy [44], and is presented in Fig. 3. The development of “Amigos de Fibro (Fibro Friends)” was published and showed a good level of agreement among evaluators [45].

**Fig. 3 Fig3:**
[figure not shown]
Script of “Amigos de Fibro (Fibro Friends)”

#### Control group

Participants in the CG will receive an educational self-care e-book that was prepared by the authors themselves and that will address the same information that was defined in the construction of “Amigos de Fibro (Fibro Friends)”. The order of the themes of the e-book will be the same as presented in the experimental group. The e-book will have weekly chapters, meaning each week you should read a chapter with the information and note the start and end date of the reading. The choice of weekly chapters is for the CG to finish participating in the study at the same time as the experimental group. Moreover, once a week, the responsible physiotherapist will call each participant of this group to ask how the reading is going and to remind them to carry it through weekly.

The final version of the e-book is comprised of 90 pages, with the title “Amigos de Fibro (Fibro Friends)”: Promoting Health in Fibromyalgia”. The e-book was created using the Canva software, a graphic design platform that allows users to create different types of visual content. In addition, it features graphic illustrations taken from Envato Elements, a subscription platform for graphic design items. The material was divided into 10 blocks with the following themes: getting to know fibromyalgia (chapter 1), health promotion and care (chapter 2), family and work (chapter 3), body practices and physical activities (chapter 4), healthy and adequate nutrition (chapter 5), health and well-being (chapter 6), pharmacological approach (chapter 7), integrative and complementary practices (chapter 8), occupational performance (chapter 9), and sleep quality (chapter 10).

The educational content refers to self-care measures that promote the health and quality of life of individuals with fibromyalgia. In order to enrich the content, improve readability and general reader captivation of the e-book, and offer the target audience the opportunity to delve deeper into the topic, references, and links were added to the end of the material, which give access to the entirety of articles, books, theses, and websites that also support the material’s theoretical framework. The e-book has already been validated and published and showed a good level of agreement among evaluators [31]. The final version of the e-book is available at http://www.amigosdefibro.com.br.

### Criteria for discontinuing or modifying allocated interventions {11b}

There will be no special criteria for discontinuing or modifying allocated interventions.

### Strategies to improve adherence to interventions {11c}

Once a week, the responsible researcher will call each participant to ask how the reading is going and to remind them to do it weekly (control group). In the intervention group, adherence will be analyzed and, if necessary, the researcher in charge will also call to find out the reason for the absences from the intervention.

### Relevant concomitant care permitted or prohibited during the trial {11d}

Implementation of the control group with a self-care educational e-book versus web-based educational intervention “Amigos de Fibro (Fibro Friends)” will not require change in usual care pathways (including the use of any medication) for the treatment of fibromyalgia and these will continue for both study arms.

### Provisions for post-trial care {30}

At the end of the project (end of the 12 months of follow-up), all participants will be invited to participate in the groups in which they were not selected, in order to thank all participants in the research.

### Outcomes {12}

Participants will be evaluated pre- and post-intervention by a blind evaluator, previously trained to obtain information and confirm eligibility criteria, in addition to primary and secondary outcomes. The evaluator will be asked to guess which group the participants were in (intervention or control) at the end of the study to measure the blindness of the evaluator. Due to the nature of the interventions, it will not be possible to blind neither the responsible participants nor professionals towards the application of the web-based intervention.

#### Main outcome variable

##### Quality of life

The Fibromyalgia Impact Questionnaire (FIQ) was first developed by Burckardt, Clark, and Bennett [46], and translated and adapted to the Brazilian population by Marques et al. [47], reviewed by Bennett et al. [48] and validated for Brazil by Paiva et al. [49] will be used. This tool has been demonstrated to be trustworthy and valid. The FIQ is a change-sensitive and clinically measurable tool [50], which has good discriminative power, with high sensitivity and specificities (78.2 and 81.2%, respectively) [51]. Other aspects of these tools are also important, such as applicability, practicality, and clarity [50]. This tool consists of 19 questions, organized into 10 items: functional capacity, well-being, work absences, workability, pain, fatigue, morning tiredness, stiffness, anxiety, and depression [47]. Item 1’s value can range from 0 to 30, and items 2 and 3’s values can range from 0 to 7. The remaining items are composed of visual analog scales ranging from 0 to 10. To obtain the tool’s score, item 2 must be recorded (0–7, 1–6, 2 = 5, 3 = 4, 4 = 3, 5 = 2, 6 = 1, and 7 = 0) and normalized on a scale of 0 to 10. Items 1 and 2 must also be normalized, so that all the items are expressed in similar units [47]. The total FIQ score will be obtained by the sum of the items, ranging from 0 to 100. The highest values indicate a greater impact of fibromyalgia in quality of life. The total score will also classify impairment as mild (0 to 38) or severe (59 to 100) [47].

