**Methods:**

A study with a randomized controlled trial approach will be carried out. The sample will consist of 24 participants, divided into two groups, with 12 individuals each. The experimental group will participate in meetings with lectures, debates, conversation rounds and exercises by a multidisciplinary team. Physical exercises will also be performed in an online environment. On the other hand, the control group will receive an e-book of education and self-care. Primary outcomes will be quality of life. The secondary outcomes will be sociodemographic and health profile, pain intensity, sleep quality, self-care agency, usage and costs of health and social care services, viability of the program and program participation. In addition, a qualitative evaluation process will be carried out with the participants. After the intervention, the data of both groups will be collected again, as well as after 3, 6, and 12 months to verify the effect and the maintenance of the intervention.

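### The FIQ scoring rule for the primary outcome names item 2 twice and never names item 3, so the total as written runs 0 to 97 rather than the stated 0 to 100

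*Protocol article*

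**What the plan says.** The abstract of the protocol article states "Primary outcomes will be quality of life", and the section on the main outcome variable (Quality of life) makes the FIQ the instrument for it. That section describes the scoring as follows:

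- Structure: "This tool consists of 19 questions, organized into 10 items". Work absences comes third in the list of items.
- Raw ranges: "Item 1’s value can range from 0 to 30, and items 2 and 3’s values can range from 0 to 7". Then: "The remaining items are composed of visual analog scales ranging from 0 to 10".
- Item 2 is reversed (0 becomes 7, and so on down to 7 becomes 0) "and normalized on a scale of 0 to 10".
- Next: "Items 1 and 2 must also be normalized, so that all the items are expressed in similar units".
- Total: "The total FIQ score will be obtained by the sum of the items, ranging from 0 to 100".
- Classes: "The total score will also classify impairment as mild (0 to 38) or severe (59 to 100".

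No other section of the article repeats or corrects this rule. The section on plans for assessment and collection of outcomes refers the reader back to the methodology section for the details of the instruments.

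**The concern.** Three of the ten items are not on a 0 to 10 scale when collected: items 1, 2 and 3. The text deals with item 2, then says that items 1 and 2 need the same treatment. Item 3 is left on 0 to 7. The rule therefore contradicts its own stated purpose (all items in similar units) and its own stated range (0 to 100).

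The matter deserves attention because this is the primary endpoint and because the rule will be applied by people outside the team. The data management section gives the organisation of the data to an independent researcher, and the statistical section says that the analysis is not done by a member of the study group. Someone who codes the sentence as written would produce a total that gives work absence less weight than every other item.

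The error would not be a constant offset. It depends on the answer to item 3, so it can change the order of participants, and the planned between-group tests are non-parametric with 12 participants per arm.

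A lesser point is that the two severity classes do not cover the scale.

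**Working it through.** **Inputs**, all from the Quality of life section: item 1 has a raw maximum of 30, items 2 and 3 have 7 each, and items 4 to 10 are seven scales with a maximum of 10 each, together 70.

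**The plan's own figure.** The stated range is 0 to 100. To see which scaling reproduces it, take the sum of the item maxima, with a scaled item having maximum 10:

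maximum = 30 + 7 + 7 + 70 = 114 with nothing scaled. Scaling item 1 changes this by 10 − 30 = −20. Scaling item 2 or item 3 changes it by 10 − 7 = +3 each.

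| Items scaled to 0–10 | Maximum total |
|---|---|
| none | 114 |
| 1 only | 114 − 20 = 94 |
| 2 only | 114 + 3 = 117 |
| 3 only | 114 + 3 = 117 |
| 1 and 2 (as written) | 114 − 20 + 3 = 97 |
| 1 and 3 only | 114 − 20 + 3 = 97 |
| 2 and 3 | 114 + 3 + 3 = 120 |
| 1, 2 and 3 | 114 − 20 + 3 + 3 = 100 |

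Of the eight combinations, only the last gives the stated 100. The rule as written gives 10 + 10 + 7 + 70 = 97.

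**Effect on one participant.** Let d be the value of item 3, from 0 to 7.

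- Correct contribution: d × 10/7, that is 1.43 points per unit, at most 10.
- Literal contribution: d × 1, at most 7.
- Loss: d × (10/7 − 1) = d × 3/7 = 0.43 points per unit. This is 0 at d = 0 and 3 at d = 7.

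Item 3 thus carries 7/10 = 70% of the weight of each other item.

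**Effect on ranks.** Take one participant with d = 7 and another with d = 0. If the first has the higher correct total by less than 3 points, the literal rule reverses their order.

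**Effect on the cut-offs.** A correctly scored 59 with d = 7 becomes 59 − 3 = 56 and drops out of the severe class.

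**Severity classes.** The classes end at 38 and restart at 59. The whole-number scores without a class are 39 to 58, which is 58 − 39 + 1 = 20 of the 101 values from 0 to 100. Because the scaled items need not give whole numbers, the gap is strictly everything above 38 and below 59.

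**The case against.** The strongest reply is that the paragraph largely corrects itself. Item 3's range is stated a few lines earlier, the purpose of the scaling is given in the same sentence, and the next sentence fixes the total at 0 to 100. Item 2 has already been dealt with, so a second mention introduced by *also* reads as a one-digit slip for items 1 and 3. A scorer who followed the letter would break two other statements in the same paragraph. Even then the loss is at most 3 points out of 100, is 0 for anyone with no work absence, and arises under one rule in both arms and at every visit. Rank tests and medians move only where such small shifts change an order or the median. All of this stands, and it limits the size of the point. It does not make the sentence right.

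Three stronger readings are tempting, and the document does not support them.

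- *Item 2 is to be scaled twice.* Multiplying by 10/7 a second time would take item 2 to 10 × 10/7 = 14.3 and the total to 10 + 14.3 + 7 + 70 = 101.3. But the text asks for item 2 to be put on a 0 to 10 scale. Putting an item that is already on 0 to 10 onto 0 to 10 changes nothing, and no sentence asks for a second factor.
- *More than one version of the FIQ is in play.* The paragraph cites a development paper, a translation, a later review and a Brazilian validation. It nevertheless describes one structure and one scoring scheme, and the abbreviation list has one FIQ. Whether the other cited papers score differently cannot be settled from this document.
- *The gap between the classes damages the primary analysis.* The statistical methods section names no comparison by severity class, and the section on additional analyses says that nothing further is planned.

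**Conclusion.** The scoring sentence is wrong as written. It yields a total of 0 to 97 where the protocol states 0 to 100, because item 3 is not named for scaling. The size is modest: 0 to 3 points per participant, depending on the answer to item 3, with that item carrying 70% of its intended weight. The most likely explanation is a slip for items 1 and 3. This rests on the stated range and the stated purpose, which only one of the eight possible scalings satisfies. It would be wrong to infer that the primary endpoint is undefined or that the trial's comparison is invalid, because the intended rule can be recovered from the paragraph itself.

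The missing class between 38 and 59 is a secondary gap in description. The document gives no label for it, so none is assumed here.

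**What to change.** Replace the scaling sentences with an explicit rule:

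- item 1 × 10/30;
- item 2 reversed (7 minus the value), then × 10/7, once;
- item 3 × 10/7;
- items 4 to 10 as recorded;
- total = sum of the ten, range 0 to 100.

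Check that the scoring code does the same: entering the worst answer to every item should return exactly 100, and the best answer exactly 0.

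For the classes, the sponsor should state what applies between 38 and 59, including how fractional scores next to each cut-off are assigned, or say why that range is left out.

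The cost is a few words in the protocol and one line of scoring code. No new data are needed, since the raw item responses are collected in any case.
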